### Consent procedure

The study nurse will seek written informed consent at the initial home visit to each potential participant, explaining the study in detail and answering any questions. Consent will be sought for the following aspects of the study:

• Practising of daily home exercises, and keeping of a daily exercise diary.

• Study nurse visits in weeks 1, 6 and 12 of the study (Figure 2), involving measurement of quadriceps strengths, degree of knee flexion and standing balance, and completion of a self-report questionnaire, taking 10-20 minutes.

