### Interventions

In each case the study intervention will last for 12 weeks. Three exercise packages have been developed with reference to published literature (one for each of the three target impairments): one for quadriceps strengthening, one for knee flexion stretches, and one for balance retraining. These exercise packages systematically progress each of the exercises through photographically-illustrated stages. Details of the packages are available as Additional files 1, 2 and 3. Participants will be assigned to receive one or more of these exercise packages, based on whether their measurements for either leg for the corresponding target impairments fall below the thresholds in Table 1. The exercises will be selected and the level-of-difficulty tailored to the abilities of the individual participant on the basis of the assessment by a study physiotherapist during the first physiotherapist home visit. This assessment will consist of a standardised clinical history taking and physical assessment, together with measurement of the target impairment(s). Selection and tailoring of the exercises will take the following factors into account:

• The presence and degree of the three impairment(s).

• The safety of the participant.

• Participant ease of performance when practising the exercises under the supervision of the physiotherapist.

• The preferences, motivations and concerns of the individual participant.

The dosage and frequency of the exercises will be decided by negotiation with the individual participant. The physiotherapist will also employ the following elements of advice and reassurance when teaching the exercises to the participants:

• Explicit identification of activities of daily living that could be improved by an improvement in the identified impairment(s).

• Education regarding the importance of strong quadriceps and/or good flexion range of motion and/or good balance both to the health of the knee joints and to overall function.

• Advice and reassurance regarding the expected adverse effects of the exercises, such as temporary pain and stiffness, including advice about the benign nature of these side-effects and the use of ice, heat and simple analgesia to manage them.

• Reassurance that the individual can contact one of the study physiotherapists by telephone at any time regarding any queries or concerns.

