#### Sensitivity analyses

To explore the potential contribution of regression to the mean, data on the three impairment measures collected for our participants at the baseline, 3-year and 6-year clinical assessment study clinics [23] will be compared to the corresponding measures taken at the initial TargET-Knee-Pain study nurse visit.

To explore the contribution of potential ceiling effects (i.e. how much improvement can be possible in the comparison groups, who will inevitably be starting with higher measures for the given target impairments), a definition of "lack of impairment" for each of the three impairments will be derived, based on age-gender stratified norms. The percentage of individuals who lack each of the target impairments, according to these definitions, will be determined at 12-week follow-up, and will be compared between those who were and those who were not impaired in that measure at recruitment.

To explore the effects that poor adherence with the exercise programmes may have on the results, efficacy subgroup analyses will be conducted, whereby the analyses will be repeated in the subgroup of individuals deemed to have been adherent with the exercise programmes and compared with the subset deemed not to have been adherent. For this purpose, inadequate adherence will be defined as follows:

• Not having done any of the exercises at all in the course of at least one rolling calendar week throughout the 12 week period of their involvement in the study (according to the daily exercise diaries).

• Not having done any of the exercises at all on a cumulative total of 12 days throughout the 12 week period of their involvement in the study (according to the daily exercise diaries).

• Participant self-report of not having done their exercises as often as they were advised to in either the 6 or 12 week questionnaires.

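### The fixed 12-day diary criterion does not fit a negotiated exercise frequency: a participant who agreed five or fewer exercise days a week and did every session can be classed as inadequately adherent

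*Protocol article*

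**What the plan says.** Three places in the Protocol article bear on this.

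- **Sensitivity analyses.** The analyses are to be repeated in participants deemed adherent and compared with those deemed not adherent. Inadequate adherence is defined by three criteria, listed without an 'and' or an 'or':
  - a gap, "Not having done any of the exercises at all in the course of at least one rolling calendar week";
  - a cumulative count, "Not having done any of the exercises at all on a cumulative total of 12 days", taken from the diaries over the 12 weeks;
  - a self-report, "Participant self-report of not having done their exercises as often as they were advised to in either the 6 or 12 week questionnaires".
- **Interventions.** "The dosage and frequency of the exercises will be decided by negotiation with the individual participant". No section sets a seven-day schedule or a minimum number of exercise days a week.
- **Consent procedure.** Consent is sought for "Practising of daily home exercises, and keeping of a daily exercise diary", which points towards a daily default.

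**The concern.** Adherence means doing what was agreed. The cumulative criterion does not refer to what was agreed; it counts days on which nothing was done. On a daily plan the two are the same, because every exercise-free day is a missed day. On a plan with rest days they differ, because planned rest days count against the participant.

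The self-report criterion uses the other yardstick, what the participant was advised to do. One person can therefore satisfy it in full and still fail the day count.

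At stake is the meaning of the adherent and non-adherent subgroups. Full adherers on less-than-daily plans would leave the subgroup meant to show results in people who followed the programme, and would join its comparator. The Interventions section also says that tailoring takes account of impairment, ease of performance, preferences and concerns. If those shape the agreed frequency too, the label would partly reflect them as well as compliance.

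**Working it through.** **Inputs**

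- Duration: "In each case the study intervention will last for 12 weeks" (Interventions), so 12 × 7 = 84 days.
- Threshold: 12 exercise-free days (Sensitivity analyses). It is a definition with no stated derivation, so there is no figure to reproduce. It equals 12/84 = 14.3%, or one day in seven.
- Agreed exercise days per week, *f*: not fixed (Interventions). An exercise day here is a day with any exercise at all, as the criterion is worded.

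**Exercise-free days when every agreed session is done**

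Formula: 12 × (7 − *f*).

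| Agreed days per week | Exercise days | Exercise-free days | Flagged if 12 or more | Flagged if more than 12 |
|---|---|---|---|---|
| 7 | 84 | 0 | no | no |
| 6 | 72 | 12 | yes | no |
| 5 | 60 | 24 | yes | yes |
| 4 | 48 | 36 | yes | yes |
| 3 | 36 | 48 | yes | yes |

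Read as 12 or more, staying clear of the threshold needs at most 11 exercise-free days, that is 84 − 11 = 73 exercise days, or 73/12 = 6.08 a week. By the day count alone, a participant on a daily plan may miss 11 sessions (11/84 = 13%) and pass, while one who agreed five days a week and missed none fails.

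**How firm the boundary is**

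Suppose the days that count number 77 to 83, for example because days before the exercises are first taught are left out (an assumption; the article does not fix this). With *w* such days, the count is *w* × (7 − *f*)/7:

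- *f* = 6: 77/7 = 11.0 to 83/7 = 11.9, below 12.
- *f* = 5: 77 × 2/7 = 22.0 to 83 × 2/7 = 23.7, still well above 12.

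So six days a week is caught only if 12 itself triggers and all 84 days count. Five or fewer is caught under each of these variants.

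**How many participants could be affected**

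The article does not give the share who agree five or fewer days a week. Call it *q*, an assumption. Of the planned 60 participants, 60*q* would be flagged even with perfect compliance: 0 at *q* = 0, 15 at 25%, 30 at 50%, 45 at 75%. This is a range, not an estimate.

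**Check of the replacement rule (one-seventh or more of agreed days missed)**

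- 7 days a week: 84/7 = 12, so flagged at 12 missed, which matches the present threshold read as 12 or more.
- 6 days a week: 72/7 = 10.3, so flagged at 11 missed.
- 5 days a week: 60/7 = 8.6, so flagged at 9 missed.
- 3 days a week: 36/7 = 5.1, so flagged at 6 missed.
- Every agreed session done: 0 missed at any frequency, never flagged.

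**The case against.** The strongest reply is that the programme may be daily. Consent covers daily home exercises and a daily diary, and a negotiated dosage and frequency could mean repetitions, sessions per day, or how often each exercise in the package is done. On that reading the 12-day rule is a sensible tolerance of one day in seven. The article gives no example of a plan below seven days a week. This stands in part: such plans may be uncommon, and if there are none the rule works as intended. But nothing in the Interventions section restricts the negotiation to within-day matters, so the rule has to work for what that section allows.

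The criterion is also more lenient than it first looks. Someone who rests from strengthening but does a stretch that day is not counted. That stands too, and it is why the table concerns days with no exercise at all.

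If all three criteria had to be met together, a full adherer would not be mislabelled. The text does not say how they combine. Each reads as a description of inadequate adherence on its own, so any-one-suffices is the natural reading, but it remains a reading.

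One could also defend classifying by exercise days actually done, as a measure of exposure. The article, however, presents the label as adherence with the exercise programmes, and its third criterion, "Participant self-report of not having done their exercises as often as they were advised to", is relative to advice.

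Two stronger inferences are tempting. A reader might infer that everyone on six days a week is misclassified; the boundary check shows that this is not established. A reader might also infer that the comparison is biased towards zero by a calculable amount. That needs a known share on less-than-daily plans, a known true adherence rate unrelated to agreed frequency, and equal benefit at every frequency. The article supplies none of these. If agreed frequency follows pain or ability, the bias could go either way.

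**Conclusion.** The point holds, limited to the adherence sensitivity analysis. A fixed count of exercise-free days does not measure adherence when the agreed number of exercise days can differ between participants. If any one criterion suffices, a participant who agreed five or fewer days a week and did every session has 24 or more exercise-free days against a threshold of 12 and is put in the wrong subgroup. Six days a week is a boundary case.

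The number affected and the direction of any bias depend on how many less-than-daily plans are agreed, which the article does not state; the effect is nil if all plans are daily. The primary analysis selects participants by the exercise package they receive, not by this label, so it is unaffected. The matter deserves correction because the rule is stated explicitly and is cheap to put right, not because it threatens the main result.

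**What to change.** 1. Reconcile the Consent procedure (daily), Interventions (negotiated) and Sensitivity analyses (fixed count), so that it is clear whether plans with exercise-free days can be agreed. No exercise frequency is proposed here.
2. Replace the cumulative criterion with missed agreed exercise days: adherence is inadequate when one-seventh or more of the agreed exercise days over the 12 weeks are missed. For each week, missed days are the agreed days minus the days with any exercise in the diary, not below zero. Take the agreed frequency from the notes made at each physiotherapist contact, so that changes during the programme are followed.
3. State which days count, in particular whether days before the exercises are first taught are included.
4. State that meeting any one of the three criteria is sufficient.

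The cost is one extra recorded field, a sentence or two in the analysis section and slightly more analysis work. The Interventions section already has every physiotherapist contact written up in a standardised booklet, so no new contact is needed. For anyone on a daily plan the rule stays as it is now, read as 12 or more of 84 days.

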#### Secondary analyses

To investigate whether improvements in the target impairments are reflected in improvements in self-reported knee pain, stiffness and functional difficulties, mean changes (or their non-parametric equivalents, depending on the distribution of the change values) in the corresponding WOMAC subscale scores, between baseline and 12 weeks, will be calculated across all individuals, irrespective of which impairments they received exercises for. Associations between changes in the target impairments and changes in the WOMAC subscales will be examined by calculating Pearson's product-moment correlation coefficients (or their non-parametric equivalents, depending on the distribution of the change values).

To investigate whether improvements in self-report measures of pain, stiffness and physical function will be greater amongst those participants receiving exercises targeted at more than one impairment than amongst those participants receiving exercises targeted at only one impairment, mean differences in WOMAC change scores for the three subscales (or their non-parametric equivalents, depending on the distribution of the change values) will be calculated for both of these groups and compared across them.

To investigate the feasibility of this intervention and its acceptability to patients, responses to free-text and Likert-response-type questions will be analysed. This will include questions about barriers to adherence to the exercise programmes, and questions soliciting participants' views regarding participation in the study and the ways in which they believe that things could be improved. Analyses will include frequency counts of the various responses to Likert-type questions and a thematic analysis of free-text responses in the 12 week questionnaire.

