## Methods/Design

### Design

Single-centre, uncontrolled before-after study.

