### Sample

The sampling frame for this study will be existing participants in an established observational cohort study of knee pain and osteoarthritis, known as The Clinical Assessment Study of the Knee - CAS(K) [23,24]. CAS(K) participants were originally recruited from the registers of three general practices in North Staffordshire between 2002 and 2003. All were aged 50 years and older and reported knee pain within the previous 12 months. Participants have been followed up at 18-month intervals. We aim to recruit 60 participants to our study from a conservatively estimated population of 314 due to attend for repeat follow-up six years after their baseline assessments. Power calculations, based on observed effect sizes in previous trials of exercises for patients with OA of the knee, suggest that a sample size of 60 individuals would be capable of detecting an 8° improvement in the degree of knee flexion or an 8 Kg improvement in quadriceps strength with approximately 86% power, given a Type 1 error rate of 5% [25,26].

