### Eligibility criteria

Potential participants in our study will be attendees at the CAS(K) 6-year-follow-up research assessment clinics, who are men and women, all aged 56+ years with a history of knee pain. To be included in this study, they will have measurements for at least one of the target impairments (quadriceps strength, degree of knee flexion and single-leg standing balance) that fall below the lowest quartile of age- and gender-stratified values recorded at the baseline assessments between 2002 and 2003 (Table 1). In order to be considered for inclusion in the study, individuals must be willing and able to commit to a programme of exercises for a 12-week period.

**Table 1 T1:** Age and gender thresholds for study inclusion

	Male	Female
Range of knee joint flexion		
55-64 years	< 128°	< 127°
65-74 years	< 125°	< 122°
75+ years	< 120°	< 117°
		
Isometric quadriceps strength (kilograms force)		
55-64 years	< 18.1	< 11.3
65-74 years	< 17.2	< 9.4
75+ years	< 13.9	< 9.0
		
Single-leg standing balance (seconds)		
55-64 years	< 8	< 5
65-74 years	< 3	< 3
75+ years	< 2	< 2

The exclusion criteria are: total knee replacement of either knee joint; an existing diagnosis of inflammatory arthropathy; lower limb weakness from neurological conditions; receiving medication that adversely affects standing balance; open wounds on the anterior aspect of either distal shin; a self-report of unstable angina or uncontrolled hypertension/hypotension; an inner ear problem that compromises standing balance; no mobile or home telephone; unavailability for fortnightly home visits or telephone contact for the whole of a given working week of their potential involvement in the study; an inability to transfer independently from lying to sitting or from sitting to standing; currently receiving physiotherapy for their knee problem.

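### The comparison of raw WOMAC change between participants with several targeted impairments and those with one takes no account of where the two groups start, so a difference can be misread as a benefit of more exercise packages

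*Protocol article*

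**What the plan says.** The protocol article describes the study as a "Single-centre, uncontrolled before-after study" (Design) with a target of 60 participants (Sample). Under Interventions, packages follow the participant's own measurements: "Participants will be assigned to receive one or more of these exercise packages, based on whether their measurements for either leg" fall below the Table 1 thresholds. The number of packages is therefore the number of impairments, and nobody is randomised to one or several.

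Under Secondary analyses, the article asks whether improvement in WOMAC pain, stiffness and function is greater in those "receiving exercises targeted at more than one impairment than amongst those participants receiving exercises targeted at only one impairment". Mean changes on the three subscales, or non-parametric equivalents, "will be calculated for both of these groups and compared across them". Neither a baseline WOMAC term nor any other covariate is named for this comparison.

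Under Sensitivity analyses, the authors plan one check on regression to the mean and one on how far the comparison groups can improve. Both are confined to quadriceps strength, knee flexion and balance. Neither covers WOMAC.

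**The concern.** The group with more than one package is, by construction, the group with more impairments. The Background says these impairments go with pain and disability, so on the study's own rationale this group may start with worse WOMAC scores. Entry asks for people "all aged 56+ years with a history of knee pain" and at least one impairment below threshold. No minimum current pain or WOMAC score is required, and the cohort's pain criterion dates from recruitment in 2002 to 2003. Some participants may therefore start near the best possible score and have little room to improve. If that is commoner in the single-impairment group, its raw change is held down for reasons unrelated to the number of packages.

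At stake is the reading of one secondary result. An apparent gain from adding packages could shape the design of the randomised trials that the Discussion has in view.

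**Working it through.** **The plan's own figure.** The only power statement (Sample) is that 60 people are "capable of detecting an 8° improvement in the degree of knee flexion or an 8 Kg improvement in quadriceps strength" with about 86% power at a 5% type 1 error. No SD is given, so it can be neither reproduced nor refuted. By normal approximation it implies an SD of 20.4 for a one-sample change in 60 people, or 10.2 for a two-sided comparison of 30 with 30. It concerns the impairments, not WOMAC, and nothing below depends on it.

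**Inputs.** From the article: 60 participants, groups set by impairment number, raw change analysed. Assumed, because the article does not give them: baseline WOMAC gap D = 0 to 0.8 SD (multi-impairment group worse), baseline to 12-week correlation r = 0.5 to 0.7, equal SDs, and splits of 30/30 or 20/40.

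**Case A: 12-week WOMAC depends only on baseline WOMAC, and package number has no effect.**
- Spurious extra improvement in raw change = D − rD = (1 − r)D.
- SD of change = √(2(1 − r)); SE = that SD × √(1/n₁ + 1/n₂).
- Example: r = 0.5, D = 0.5, 30/30. Bias = 0.5 × 0.5 = 0.25 SD. SD of change = 1. SE = √(2/30) = 0.258. Noncentrality = 0.25/0.258 = 0.97. The two-sided 5% t-test on 58 degrees of freedom then rejects in 15.9% of studies.

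| Split, r | D = 0 | D = 0.3 | D = 0.5 | D = 0.8 |
|---|---|---|---|---|
| 30/30, 0.5: bias (SD); false positives | 0; 5.0% | 0.15; 8.8% | 0.25; 15.9% | 0.40; 33.2% |
| 30/30, 0.7 | 0; 5.0% | 0.09; 7.3% | 0.15; 11.4% | 0.24; 21.9% |
| 20/40, 0.5 | 0; 5.0% | 0.15; 8.4% | 0.25; 14.6% | 0.40; 30.1% |

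Regression on baseline (ANCOVA), simulated 20,000 times in each of four of these settings, had bias near 0 and 4.9% to 5.2% false positives.

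**Case B: the gap is a stable difference between the groups, and package number has no effect.** With r = 0.5, D = 0.5 and 30/30, simulation gave 0.00 SD for raw change and −0.25 SD for ANCOVA. The bias is of the same size as in Case A, but now sits in the adjusted estimate and points against the multi-impairment group.

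**Between the two.** If a fraction k of the gap would persist with no package effect, raw change is off by (1 − k)D and ANCOVA by −(k − r)D. The two estimates differ by (1 − k)D + (k − r)D = (1 − r)D whatever k is. For k between r and 1 they lie on either side of the truth. With r = 0.5, D = 0.5 and k = 0.75 they are off by +0.125 and −0.125 SD. Outside that range both can err in the same direction.

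**Precision.** Adjustment multiplies residual variance by (1 − r²)/(2(1 − r)) = (1 + r)/2, which is 0.75 to 0.85 for r = 0.5 to 0.7. The gain for the group contrast is smaller, because group and baseline are correlated. At 30/30 and D = 0.7 the inflation is 1 + 0.25 × 0.49 = 1.12, so at r = 0.7 the ratio is 0.85 × 1.12 = 0.95.

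**The case against.** The strongest reply is that the groups are not formed on WOMAC. Eligibility rests on impairments measured at the cohort clinic, while WOMAC is self-reported later, at the first nurse home visit. Random error in baseline WOMAC has no clear route into group membership, and a gap that comes from having more impairments could be largely stable. Raw change would then be unbiased and ANCOVA would create the error it was meant to remove. This stands. A reader might infer that the planned contrast must favour more packages through regression to the mean and floor effects alone, and that ANCOVA should replace change scores. The article does not support either inference.

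It also stands that no WOMAC distribution is reported, so single-impairment participants near the best possible score are a possibility, not a fact. Everyone must have at least one impairment, which makes symptom-free participants less likely. A linear baseline term would not properly correct a floor effect in any case.

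It can further be said that the article names no test and that covariates may be set in an analysis plan that is not at hand. This carries less weight. The article itself fixes change scores, or non-parametric equivalents, as what is compared, and it recognises the same two problems for the impairments without extending its checks to WOMAC.

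**Conclusion.** The point holds in a limited form. The planned comparison contrasts raw WOMAC change between non-randomised groups that may well start at different levels, and nothing else in the article guards against misreading the result. The size and direction of any bias depend on a baseline gap that is not reported and on whether that gap is stable. Under the assumptions shown (gaps of 0.3 to 0.8 SD, r of 0.5 to 0.7), it is 0.09 to 0.40 SD in favour of more packages if follow-up depends only on baseline, and zero if the gap is stable or absent. These are illustrations, not estimates for this study.

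No analysis of these data can separate package number from impairment number. As this is one secondary comparison in a proof-of-principle study, and the primary conclusions do not depend on it, the change is a low-cost improvement and not a correction on which the study turns.

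**What to change.** Under Secondary analyses, for each WOMAC subscale:

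1. Report baseline scores by group, including the share near the best possible score.
2. Report the raw difference in change with a 95% CI, as now planned.
3. Alongside it, report a prespecified regression of the 12-week score on group, baseline subscale score, age and gender, with a 95% CI for the group difference.
4. State beforehand that a conclusion will be drawn only if both estimates agree, and that it will be described as an exploratory association, because package number and impairment number cannot be separated.

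The cost is a few sentences of wording and slightly more analysis. Baseline WOMAC is already collected at the first nurse visit, and age and gender are already used for the Table 1 thresholds. The downside is a softer claim and two estimates that may differ, since neither is guaranteed unbiased in non-randomised groups.
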